### Values condition

The values intervention is delivered as two components: Activities to support values clarification and commitment delivered on day three of training; and values-based coaching using CRM tools for 12 months within the workplace.

The aims of the values condition include:

1. Increase awareness of the values in which CRM is embedded.

2. Increase the extent to which the personal and professional values of the staff are explicit and expressed in the workplace.

3. Create opportunities for individual staff to identify the overlap or concordance of the CRM with their own values.

4. Regular and sustained (12 one-hour sessions each month) investment in the professional and personal development of staff via clarification and commitment to values-based goal-setting using CRM tools as the framework.

### Protocol for day three values intervention

The one-day values intervention is experiential in nature, using a structured values-clarification exercise with demonstrated utility in a range of clinical and non-clinical settings [36]. The purpose of this task is to help participants identify what values are most important to them, and to increase their awareness of the potential to actively pursue valued directions in both personal and professional domains of their life (*i*.*e*., increase the extent to which values are consciously used as a driver of purposeful behaviour). Staff members will be exposed to the concept of values in the standard CRM training (days one and two), and will have a basic theoretical and operational understanding of both the merit and applicability of working with values generally. Additionally, a focus on related concepts of willingness and commitment [37] that have been emphasised as important to values work will follow in day three.

Participants are given a set of 60 cards, each featuring a specific principle of living that is associated with a universal value-domain as outlined in Schwartz’ model [38,39]. They are then facilitated through a structured sorting task that titrates their focus down to the 15 valued directions each individual identifies as ‘most important to them.’

Following the card-sorting task, an additional intervention component is employed to foster intent and commitment to take purposeful steps toward valued areas of living. In this stage, the focus is on ‘life in general,’ and participants are asked to rate the extent to which they have purposefully been trying to enact a variety of values in the past 12 weeks. They rate their subjective success at moving toward each of the 15 specific valued directions identified as ‘most important.’ This process is structured around a worksheet based on the Personal Strivings methodology developed by Sheldon *et al*. that has been used extensively within the goal setting research [35,40].

Participants are facilitated through this process a second time, adopting a workplace focus. Participants are given the instruction; ‘conduct the card-sorting task again, this time focusing on what is most important to you in your current job.’ Following this, participants complete a second worksheet to rate the intent and self-reported success of recent striving toward the work values they have identified as most important at work.

The components thereafter focus on increasing awareness of the potential concordance between personal and professional values through a facilitated discussion session. Participants are invited to discuss commonalities between their ‘life in general’ list and their ‘workplace’ list. They are then asked to identify ways they can bring their ‘life in general’ principles into their workplace before being facilitated through the completion of the specific CRM values tool (known as the ‘camera’ [41]) as an initial commitment to this process.

### Protocol for values coaching

Individual coaching sessions adopt a structure known as the GROW model structure in both conditions. GROW was made popular by Graham Alexandar and John Whitmore and it is widely used in organisational and coaching contexts as a method of setting a basic frame to a coaching session [42]. It is particularly attractive in this case due its accessibility to those with little or no prior coaching experience. GROW is an acronym for the basic components of a coaching session—namely, goal, reality, options, wrap up/where to.

Individuals identified as suitable coaches within each partner organisations will be referred to a further half-day of coaching training conducted by the research team. Potential coaches are identified by managers within each of the organisations and also through a call for expressions of interest. Trained coaches are assigned to mental health workers within the same experimental condition, but outside line management to increase role clarity. Coaching consists of 12 hour-long sessions scheduled once per month and conducted in the course of paid working hours for both participants. The CRM tools are used as the framework for recording and structuring the recipients’ development across the coaching period, such that the participating staff members are using the tools that are part of the organisational change initiative themselves (*i*.*e*., in relation to their own values-based goals). The particular focus within the values condition is on the establishment of work-related goals that fit with the values stated by the recipient in initial training, and clarified as the coaching process continues.

### Implementation condition

The delivery of the implementation condition intervention components follow the same format as in the values condition but differ in focus and content. The day three of training in the implementation group is experiential in nature, but focuses on addressing opportunities for and barriers to the implementation of the CRM into practice within the workplace. The methodology used to structure and support the implementation intervention is the ‘Strengths, Weaknesses, Opportunities, and Threats (SWOT) Analysis’ developed by Albert Humphrey and used extensively in organisational contexts [43,44].

Coaching in the control condition is consistent in format and overall structure to the values condition. Implementation coaching adopts an alternate focus on identification and resolution of issues related to implementation of CRM in the workplace as identified by participants. For example, pragmatic issues (*e*.*g*., addressing technical issues associated with new practices) or attitudinal issues (*e*.*g*., working through resistance to change from clients or colleagues).

The aims of the implementation condition are as follows:

1. Ongoing exposure to and skills-based practice with the CRM.

2. Opportunity to identify and develop strategies to address factors that are impeding implementation (*e*.*g*., resistance from clients or co-workers).

3. Regular and sustained investment (12 x 1 month coaching sessions) in the professional and personal development of staff using CRM tools as the framework.

In both conditions, participants are using the same protocol and model of practice they are to use with their clients upon implementation. Coaching therefore promotes experiential learning [45] in both conditions. We expect this will result in increased transfer of CRM into practice compared to our previous research. In the values condition there is an additional parallel process such that mental health staff will be actively encouraged to work with the CRM practices in relation to their own lives and values, just as their clients would. That is, they are applying both the practices and the underlying processes ‘for real’ (values), rather than just practising in the use of the CRM (implementation). The value of parallel relationships in transferring knowledge from one dyad (*e*.*g*., supervisor and clinician) to another (*e*.*g*., clinician and client) has been elaborated within counselling literature [46]. We hypothesise this additional parallel relationship will increase implementation as a result of enhanced sense of meaning and connection with the CRM such that it becomes more internalised [47].

### Data collection and handling

The study will last 18 months with data collection at multiple times points. Primary data comprises a questionnaire battery completed by participants at five time points throughout the intervention (specific measures are outlined below). Data is also collected from coaches and recipients’ at each monthly coaching session to assess adherence to the GROW framework, integrity to experimental condition, and elements of the coaching alliance. In addition to self-reported measures of implementation, the study uses objective measures of transfer (also outlined below).

Data collection handling is in accordance with the procedures specified in the ethics approval obtained from the Human Research Ethics Committee at the University of Wollongong (HE09/221). A prime focus is on maintaining confidentiality of participants, which is promoted by the use of a unique self-generated identifier established at the first data collection point and re-used at subsequent collections. Additionally, because the research focuses on work-related variables and is being conducted in a work setting, individual data is forwarded to the research team directly (*i*.*e*., handed personally in sealed envelopes when on-site). This is to reduce possible biased responding and staff concerns that their individual information could be seen by superiors or other personnel within their organisation.

### Measures and data

The battery of measures will also include measures of intention to leave [48] job satisfaction [49], and burnout [50]. This additional data will be utilised by the research team to explore another set of hypotheses distinct from those being investigated here. Questionnaires pertaining to the outlined hypotheses are as follows.

### Staff knowledge and attitudes toward recovery

A range of questionnaires will be used to determine the knowledge, attitudes, and beliefs of participants related to the concept of recovery. These measures will be compared with previous research conducted by this team [51].

The Recovery Knowledge Inventory (RKI) [51] is a 20-item instrument that assesses mental health staff knowledge and attitudes about recovery using a five-point Likert scale. It has been used in previous research to assess pre-post change following intervention and has satisfactory psychometric properties [51].

The Staff Attitudes Towards Recovery Scale (STARS) is a 19-item measure developed and evaluated as part of the Crowe et al. study [52] and assesses attitudes and hopefulness related to the goal striving and recovery possibilities for clients. It has a five-point Likert response scale (strongly disagree to strongly agree) and higher scores reflect more hopeful attitudes. The STARS has satisfactory psychometric properties (α =.81) as established in previous work [52].

### Autonomy and values concordance

The Collaborative Recovery Model Values Questionnaire (CRM-VQ) is a modified version of the Personal Strivings questionnaire developed by Sheldon *et al*. [40]. The modification involves the use of perceived locus of causation from Sheldon’s strivings questionnaire, applied to the six components of CRM. This measure will examine the degree to which values embedded within the CRM are concordant with the personal values of participants. It will also assess the extent to which strivings toward the CRM practices are done for autonomous versus controlled (externally regulated) reasons.

### Self-reported transfer

#### CRM-VQ

This measure also includes items that assess the implementation intentions and self-reported success of acting purposefully toward the valued directions encompassed within the CRM. Items include ‘to what extent have you made specific plans about when, where, and how to put this value into play?’ and ‘In the last 12 weeks, I have been this successful in living this value,’ to which responses will be elicited on a five-point Likert scale. An additional item relating to anticipation of implementation barriers (‘to what extent have you anticipated possible distractions and obstacles to putting this value into play?’) has been included and will be rated in the same manner. This item will allow us to investigate the impact of deliberately addressing implementation barriers (control condition).

### Evidence of transfer within the workplace

Transfer indicators include time to implementation and maintenance of change. Transfer indicators will replicate those used previously by the research team [51]. We will seek direct evidence of implementation of any of the specific tools with the CRM (known as LifeJET) that are used to structure and record the recovery-focused practice of mental health workers. That is, examples of completed LifeJET documents within participant files. Time to implementation is calculated by determining the number of days lapsed between the date of training and the first date an example of completed LifeJET protocols was identified for participants. Maintenance of change is calculated by determining the proportion of staff work samples that are evidencing transfer (*i*.*e*., completed examples of CRM) after 12 months in comparison to time periods shortly after training (*e*.*g*., one month, six months).

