### Qualitative assessment of concordance between work samples and CRM values

A novel aspect of this research is the utilisation of a process-oriented protocol to assess worker adherence to the principles embedded within CRM. For example, the principle of personalisation (*i*.*e*., evidence of unique and person-centred approach to service delivery) is acknowledged as important in recovery [3]. Personalisation will be assessed across two dimensions (the content in the sample reflects unique expression of ideas; the language/presentation of content reflects individuality) using a three-point scale (0 = no, 1 = partially, 2 = yes). De-identified research copies of work samples are to be forwarded by participating mental health workers on a monthly basis by an on-site coordinator. Following power calculations, an online number generator will be used to facilitate random identification of an appropriate number of staff whose work-samples are to be reviewed. The samples of randomly identified staff will be reviewed using the six-point rating system at three time points (one month post-training, six months post-training, and 12 months post-training). Two trained assessors from within the research team will independently review the work samples for worker process and satisfactory inter-rater reliability will be established. We will compare observed adherence to CRM principles with the self-reported transfer and measures of autonomy obtained via the CRM-VQ (described above) at matching time periods (*i*.*e*., six and 12 months) during booster sessions to explore these differing elements of implementation.

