## Discussion

### Anticipated challenges

There are a number of challenges to carrying out this project due to the applied and organisational nature of this research. The schedule of intervention needs to meet standards of feasibility and pragmatism for the partner organisations, which are contributing significantly in terms of in-kind and cash contributions. Such challenges include the need to roll-out intervention components at a rate that enables partners (who are service providers) to equip and up-skill staff and accommodate the needs of new staff, which will at times put pressure on the capacity of the research team to deliver the intervention. Additionally, the need for interventions (particularly coaching) be practical and manageable has influenced the choice of methodology to be employed (*e*.*g*., GROW method to structure coaching interactions). A prime focus for the partner organisations and the research team has been ongoing sustainability of the interventions beyond the formal support of this project. This has necessitated the interventions be amenable to being ‘passed on’ to in-service champions in a train-the-trainer model, for example.

There is risk of data loss due to the multiple time points and staff turnover rates within the mental health field. Turnover of staff in mental health service organisations is up to 26% per annum [55]. These risks are being managed by allocation of a designated project coordinator within the research team, who will provide day-to-day liaison with the industry partners and take oversight of the intervention schedules and data collection. Each industry partner will identify a liaison officer who will have carriage of the coordination and scheduling responsibilities within their organisation. Our relatively large sample size anticipated for time pointone has been estimated with consideration given to the aforementioned industry attrition rate.

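### Maintenance of change is a proportion of work samples not tied to workers who had already transferred, so it cannot separate continued practice from lapses offset by new adopters or from turnover

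*Protocol article*

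**What the plan says.** In the section Evidence of transfer within the workplace, the protocol article names two indicators. Time to implementation is dated per participant, up to "the first date an example of completed LifeJET protocols was identified for participants". Maintenance is defined differently: "Maintenance of change is calculated by determining the proportion of staff work samples that are evidencing transfer", taken "after 12 months in comparison to time periods shortly after training", with one month and six months given as examples of the earlier periods. The section says that both indicators replicate those of the team's earlier project.

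Four other places bear on how that proportion behaves:

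- **Anticipated challenges:** "Turnover of staff in mental health service organisations is up to 26% per annum". The same section expects new staff during roll-out and gives data loss as a risk.
- **Qualitative assessment of concordance between work samples and CRM values:** "work samples are to be forwarded by participating mental health workers on a monthly basis". This stands under a separate measure. For the transfer indicators, the evidence is described as completed documents in participant files.
- **Values condition and Protocol for values coaching:** the values arm has "values-based coaching using CRM tools for 12 months within the workplace", and "Coaching consists of 12 hour-long sessions scheduled once per month".
- **Implementation condition:** "Coaching in the control condition is consistent in format and overall structure to the values condition".

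**The concern.** A measure called maintenance should say whether people who took up the practice kept it up. The stated formula compares two overall proportions, and the later one is not restricted or linked to those who contributed to the earlier one. Three things follow.

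1. Workers who stop can be replaced in the numerator by workers who start. Twelve months of coaching is meant to produce new adopters, so this is an ordinary course of events for the trial.
2. Someone who has left produces no 12-month sample. If leaving is related to adoption, the proportion changes although nobody who remains has changed practice. If that relation differs between arms, the arm comparison is affected too.
3. The 12-month reading comes at about the time coaching ends, and the six-month comparator lies within the coaching year. Anticipated challenges calls sustainability beyond the project's formal support a prime focus. This indicator cannot speak to that.

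At stake is the interpretation of one of the trial's named transfer indicators: a stable or rising figure could be reported as maintained practice when individual maintenance was much lower, or the reverse.

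**Working it through.** The article gives no expected rate, sample size or power for maintenance, so there is no figure to reproduce. What follows is an illustration with the article's own numbers.

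**Inputs**

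- N = 200 staff (Study design and procedure; Data analysis).
- Starting proportion 37%, the transfer rate in the earlier study (Data analysis). It is used here only as an assumed early proportion: 0.37 × 200 = 74 adopters and 126 non-adopters.
- Turnover 26% over 12 months, the upper figure in Anticipated challenges: 0.26 × 200 = 52 leavers and 148 stayers.

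**Formula**

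12-month proportion = (early adopters − adopters who leave − adopters who lapse + new adopters) / (N − leavers)

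This takes one reading per worker still employed, which is a simplification.

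**Step 1. Turnover alone, with no stayer changing practice and 52 leavers in every row**

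| Who leaves | Calculation | 12-month figure |
|---|---|---|
| All leavers are adopters | (74 − 52)/148 | 14.9% |
| Adopters leave at 26%, as do the rest | (74 − 19.24)/148 | 37.0% |
| Adopters leave at 20% | (74 − 14.8)/148 | 40.0% |
| Adopters leave at 15% | (74 − 11.1)/148 | 42.5% |
| Adopters leave at 10% | (74 − 7.4)/148 | 45.0% |
| All leavers are non-adopters | 74/148 | 50.0% |

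The first and last rows are limits. The figure moves in either direction, and does not move when leaving is unrelated to adoption.

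**Step 2. Lapses hidden by new adopters, with no turnover**

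The proportion stays at 37% when new adopters equal lapsed adopters.

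- 30% lapse: 0.30 × 74 = 22.2 workers, hidden if 22.2/126 = 17.6% of non-adopters start. Continuation among adopters is 70%.
- 50% lapse: 0.50 × 74 = 37 workers, hidden if 37/126 = 29.4% of non-adopters start. Continuation is 50%.

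This happens even when exactly the same staff are measured at both times. For instance, 40 of 100 at both readings fits all 40 continuing, or 20 stopping while 20 others start.

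**Step 3. What a per-worker count would show in the Step 2 cases**

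Take the proportion of all 200 with evidence at both times. With no lapse it is 74/200 = 37.0%; with 30% lapsed, 51.8/200 = 25.9%; with 50% lapsed, 37/200 = 18.5%. The aggregate is 37% in all three.

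**Step 4. Timing**

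Coaching is 12 monthly sessions in both arms, and the reading is after 12 months. The article does not say when coaching starts relative to training, so the last session could fall a little before or after the reading. No coaching-free interval is specified for this indicator.

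**The case against.** The strongest reply is that the article is silent on pairing, denominator, leavers and non-submitters, and that a condensed article leaves such rules to the full protocol or analysis plan. It also has features that would allow a within-worker analysis: an identifier re-used at later collections, a companion indicator dated per participant, and full-information maximum likelihood as the general missing-data method. This is right as far as it goes. A reader might infer that the comparison is unpaired and restricted to available samples; the text does not say so. But the objection does not reach the main defect. Comparing two overall proportions lets stops and starts cancel even in a fully paired, complete data set, and no missing-data method turns an overall proportion into continuation among adopters.

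Other objections stand and limit the point:

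- A reader might infer that the reading is taken while coaching is still running. The text supports only that it falls at about the end.
- A reader might infer that coaching confounds the arms. Both arms are coached in the same format, so coaching affects what maintenance means more than the contrast between arms.
- The 50% figure might be taken as the expected bias. It needs every leaver to be a non-adopter at the upper turnover rate. Nor is the 10% increase in Data analysis a yardstick for it: that concerns overall transfer against the earlier study.
- The 18-month study length might suggest that work samples from months 13 to 18 are held. No section says so; the latest stated readings are at 12 months.
- Comparing arms only among early adopters would condition on an outcome arising after randomisation. The aggregate proportion avoids that, and so must any replacement.

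**Conclusion.** The point holds as a badly fixed definition. As stated, the indicator cannot tell continued practice from lapses offset by new adopters, and turnover can shift it either way. In the illustration, a lapse of 30% or 50% among adopters is concealed by 17.6% or 29.4% new adoption. Turnover alone moves 37% to between 14.9% and 50% at the limits, and to 40% to 45% if adopters leave at 10% to 20%. These sizes rest on an assumed early proportion of 37%, the upper turnover rate of 26%, and one reading per remaining worker. They show what can happen, not what is expected.

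Bias between arms is a possibility, conditional on leaving or non-submission differing by arm; the article gives no evidence that it will. The 12-month result describes transfer at about the end of coaching and supports no statement about persistence without support. The definition should be changed; the trial's other transfer measures are not affected by this point.

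**What to change.** Classify each worker who consents at time point one as continuing, lapsed, newly adopting, never adopting or left, and report all five counts by arm.

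For maintenance, compare between arms, accounting for worksite, the proportion of all consenting staff with evidence of transfer both early (by six months) and at 12 months. Count employed staff without evidence as not maintained, and handle leavers in a sensitivity analysis. The denominator is then fixed at time point one.

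Report continuation among early adopters descriptively only, because that subset is formed after randomisation. Keep the aggregate proportion of samples for comparison with the earlier project, labelled as such. Describe the 12-month result as transfer at about the end of coaching.

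The data are those already planned, since time to implementation requires samples to be attributed to participants. The cost is a little more analysis, and a maintenance figure that may look less favourable than the aggregate.
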